## Introduction

Cystic fibrosis (CF) is a systemic disease with thick secretions affecting multiple organs, resulting in substantial health and economic burdens [1]. The leading cause of mortality in PwCF is pulmonary dysfunction, often due to secondary bacterial colonization from defective mucociliary clearance [2]. The unified airway theory suggests that similar infectious, inflammatory processes occur in both upper and lower airways, and upper airway infections may contribute to lower airway disease [1]. Most people with CF develop chronic rhinosinusitis (PwCF+CRS) from their inability to clear thickened secretions from the upper airways and paranasal sinuses, and most PwCF will demonstrate clinical or radiographic signs of sinonasal inflammation [3]. The Cystic Fibrosis Foundation (CFF) patient registry indicates that over half of adults report symptomatic sinus disease [4].

Endoscopic sinus surgery (ESS) is a treatment option for PwCF+CRS that serves to enlarge sinus openings, clear inspissated mucus, and facilitate application of topical therapies. Based on consensus guidelines, ESS is recommended for adults and children with CF with symptomatic CRS refractory to appropriate medical therapy [5, 6]. While ESS improves sinonasal symptoms and CRS-specific quality of life in PwCF+CRS [7], there is limited data evaluating ESS treatment outcomes in the era of highly effective modulator therapy (HEMT) and potential benefits of ESS in regions beyond the paranasal sinuses (**Fig 1**).

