### Baseline measures

All participants will undergo baseline history and physical examination, CT, and nasal endoscopy. Key disease factors and potential predictors will also be obtained at initial visit with rhinologist. These include: age, gender, race/ethnicity, BMI, age at CF diagnosis, genotype, ppFEV1, CFTR modulator use details, prior ESS history, pancreatic insufficiency, *Pseudomonas* positivity, nontuberculous mycobacteria infection, lung transplantation status, insurance status, income, occupation, education, enrollment site, and medication use data. To measure CRS severity at baseline, we will use endoscopic and radiographic techniques. CT images will be scored via the Lund-Mackay system [15], and diagnostic nasal endoscopy will be performed and scored according to the Lund-Kennedy scoring system [16].

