### Outcome assessments

To address objective 1, primary pulmonary outcome measure will be ppFEV_1_. Absolute values of FEV1 and FVC will be assessed as secondary spirometry measures, enabling evaluations of the FEV1/FVC ratio [17]. Forced expiratory flow at mid-lung volume (FEF25-75) is an important marker of small airway disease and will also be evaluated [18]. Secondary outcomes include the frequency of PEx (both outpatient and inpatient) and intravenous (IV) and oral antibiotic use. PEx will be defined by the Rosenfeld criteria [19]. The number of PEx, number of hospitalizations, and days of IV and oral antibiotics used will be tracked.

To address objective 2, quality of life outcome measures will include CFQ-R, evaluating CF-specific QOL [20], and the SNOT-22, evaluating QOL in subjects with CRS [21]. PHQ-9-revised will be used for depression screening [22], and the PSQI will measure sleep duration and quality [23]. CFQ will be used for cognitive assessment [24]. The HIT-6 will be utilized to determine headache severity [25]. For evaluation of olfactory function, we will use patient-reported and objective olfactory function tests. The QOD will assess the impact of olfactory dysfunction [26]. The SIT is a measure of objective olfactory function and complements the patient-reported QOD survey [27].

To address productivity loss and health utility in objective 3, the WPAI will be used to assess the impact of a specific health problem on normal work/school or daily activity [28]. Health utility value (HUV) will be quantified from the EQ-5D [29].

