### Statistical methods

For all objectives, we will verify predictive model assumptions and test goodness-of-fit, considering alternative models if needed. We will account for potential site-specific differences as fixed effects in our models. Other methods to address site clustering include mixed effects models and generalized estimating equations.

For Objective 1, mixed effects model will be used to assess the impact of ESS versus CMT on ppFEV_1_ changes at initial and subsequent visits. Fixed effects will include baseline FEV1 (FEV1 > 80% predicted, <80% and > 50%, and <50%), CF variant status, use of CFTR modulator therapy, sex, prior sinus surgery, time and treatment; patients will be treated as random effects. An unstructured variance approach will model within-subject errors, and we will explore other covariance if needed. As exploratory analysis, we will compare ppFEV_1_ from a year before enrollment to post-treatment values using the same model. Using a generalized linear model with a Poisson distribution and prior year data, we will assess the impact of ESS versus CMT on exacerbation rates and antibiotic use, complemented by descriptive statistics for sociodemographic factors.

For Objective 2, we will describe patient characteristics using summary statistics. Treatment effects on patient reported-outcome measures (CFQ-R, SNOT-22, PHQ-9, PSQI, CFQ, QOD, and SIT) will be explored via a mixed effects model, adjusting for multiple comparisons using a gate-keeping procedure and assessing for self-report bias in patient-reported outcomes by comparing them to FEV1.

For Objective 3, we will correlate productivity costs with patient demographics, disease factors, pulmonary status, and QOL impairment. We will use a mixed effects model to evaluate these outcomes.

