### Statistical power and sample size

Sample size and power were calculated using software G Power (v. 3.1). Type I error will be controlled at two-sided 5% level. Sample size calculations were initially based on our primary QOL outcome measure (SNOT-22 scores) for objective 2, given strong evidence of improvements in the literature [33]. This was then applied to objective 1. For objective 2, detecting SNOT-22 score changes pre- and post-12 months ESS requires 9 patients for 80% power. To determine changes between treatment groups over time, considering a potential 30% cross-over between ESS and CMT groups, 106 patients are needed for 80% power, as indicated by prior data [34]. Accounting for 20% potential dropouts, our recruitment target is 150 participants, with an anticipated enrollment of approximately 170 across all centers.

Regarding ESS effects on ppFEV_1_, previous mixed results complicate clear expectations to use in power calculations for objective 1. Assuming 170 participants (factoring in 20% dropout), we will have 80% power to detect a 1.6% ppFEV_1_ change for objective 1 and a 2.3% ppFEV_1_ change for objective 1 accounting for HEMT.

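### FEV1 is not a yardstick for self-report bias in sinus, mood, sleep, cognition or smell questionnaires; a real sinus benefit with flat FEV1 could be misread as bias

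*Protocol article*

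**What the plan says.** The Objective 2 paragraph of Statistical methods names the outcomes as "patient reported-outcome measures (CFQ-R, SNOT-22, PHQ-9, PSQI, CFQ, QOD, and SIT", analyses them with a mixed effects model and a gate-keeping procedure, and adds "assessing for self-report bias in patient-reported outcomes by comparing them to FEV1". It does not say how the comparison will be made or what result would count as bias.

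Four other places bear on this:

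- Outcome assessments, Objective 1: "primary pulmonary outcome measure will be ppFEV_1".
- Introduction: "While ESS improves sinonasal symptoms and CRS-specific quality of life in PwCF+CRS [7". The same section describes earlier work on pulmonary outcomes after surgery as mixed.
- Statistical power and sample size: "previous mixed results complicate clear expectations to use in power calculations for objective 1".
- Outcome assessments, Objective 2: "The SIT is a measure of objective olfactory function and complements the patient-reported QOD survey".

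For CRS severity, Baseline measures states that "diagnostic nasal endoscopy will be performed and scored according to the Lund-Kennedy scoring system". Table 3 schedules nasal endoscopy at baseline and month 6. It schedules SIT, with all the questionnaires, at baseline and months 3, 6, 9 and 12.

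**The concern.** A check for reporting bias needs an external measure of the same thing the patient reports on. FEV1 is the pulmonary endpoint of Objective 1. It does not measure sinus symptoms, depression, sleep, cognitive failures or the impact of smell loss. Disagreement between such a questionnaire and FEV1 is therefore not evidence of misreporting, and agreement is not evidence of accuracy.

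Patients choose their treatment and know whether they had surgery, so biased reporting is a serious threat to Objective 2. The propensity score and instrumental variable methods in the article are aimed at self-selection, which is a different problem. The FEV1 comparison is the only check on reporting bias that the article names. It could cast doubt on a true sinus benefit, or reassure wrongly if FEV1 happens to rise.

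The same sentence files SIT under patient-reported measures, although Outcome assessments calls it objective. This is a separate labelling slip. It matters here because SIT is the natural comparator for QOD.

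**Working it through.** The article attaches no number to this check, so there is no figure to reproduce. The argument is structural; the numbers only illustrate it.

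**1. What the check can see.** Let the true ESS-minus-CMT difference in SNOT-22 improvement be t, the extra improvement reported by ESS patients through bias be b, and the true difference in FEV1 change be f. The data show t + b and f. They separate t from b only if f is tied to t by a known relation. The article supplies none and says that expectations for FEV1 are unclear. Two studies with the same t + b and the same f look alike, whether the gain is all t or all b.

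**2. Inputs for the illustration.**

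- "Type I error will be controlled at two-sided 5% level"; 106 patients give 80% power for SNOT-22 between groups (Statistical power and sample size).
- Detectable ppFEV1 change 1.6% at 80% power with 170 participants, 20% dropout factored in (same section).
- Analysed N: 106; 150 × 0.8 = 120; 170 × 0.8 = 136.
- Assumed: 1:1 groups; correlation between the two test statistics of 0, 0.2 or 0.4; a bias flag when SNOT-22 improves significantly and FEV1 does not.

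**3. Standardised effects.**

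- SNOT-22: (1.960 + 0.842) × √(4/106) = 0.544.
- FEV1 at 1.6%: (1.960 + 0.842) × √(4/136) = 0.480.

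**4. Flag rates** (20,000 simulated studies per cell; ranges are over the three correlations):

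| Scenario | N = 106 | N = 120 | N = 136 |
|---|---|---|---|
| Genuine benefit, no FEV1 effect | 0.777–0.781 | 0.822–0.826 | 0.863–0.868 |
| Pure reporting bias, no FEV1 effect | 0.778–0.780 | 0.820–0.827 | 0.858–0.864 |
| Genuine benefit, half the detectable FEV1 effect (0.8%) | 0.580–0.613 | 0.598–0.628 | 0.606–0.638 |
| Pure reporting bias, FEV1 effect of 1.6% | 0.201–0.245 | 0.176–0.214 | 0.152–0.178 |

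Hand check at zero correlation, N = 106: SNOT-22 is significant with probability 0.80 and FEV1 not significantly better with probability 0.975, so 0.80 × 0.975 = 0.780. For the last row at N = 136: SNOT-22 power is 0.8875 and FEV1 power 0.80, so 0.8875 × 0.20 = 0.178.

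The first two rows have the same distribution by construction; they differ only by simulation error. The flag follows whether FEV1 moved, not whether patients misreported.

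**5. What a same-organ comparison would look for.** Model the questionnaire change as a + β1·ESS + β2·(objective change) + β3·ESS × (objective change). If ESS patients over-report by a constant c, β1 shifts by c and β3 does not move. The treatment term is therefore the main quantity and the interaction a secondary look; the interaction alone would miss a constant over-report.

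**The case against.** **No decision rule is stated.** The article does not say that disagreement with FEV1 will be read as bias. A reader might infer that the check will, by design, brand a true sinus benefit as bias. The text does not support that: the flag rates above rest on an assumed rule, and the real rule may be in an analysis plan not shown. This stands, so the point is that the comparison could mislead. Further detail on the rule would not repair the choice of comparator, which the article fixes.

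**FEV1 is not irrelevant to every measure.** The list begins with CFQ-R, the CF-specific instrument, and a lung measure is more defensible for whatever respiratory content it has. The Introduction also links upper and lower airway disease. This stands for CFQ-R. For the other questionnaires, a shared disease process may produce some association, but it does not make FEV1 a criterion for the accuracy of the answers.

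**The check is secondary.** It changes no estimate, endpoint, error rate or sample size. This stands. A reader might infer that the Objective 2 treatment effects themselves are invalidated; nothing in the article implies that.

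**The expected size of the SNOT-22 gain does not measure the fault.** The article's 9 patients for a pre-post change imply a standardised change of about 1.07 if a paired t-test was used. A reader might take that as the size of the problem. It is a within-ESS effect and says nothing about how the check performs.

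**Objective measures are already in the study.** SIT is paired with QOD, and biospecimen findings will be related to clinical outcomes. True, but none of these is named as a check on self-report.

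**Conclusion.** The concern holds in limited form. For SNOT-22, PHQ-9, PSQI, CFQ and QOD, comparison with FEV1 cannot separate accurate from biased reporting, and the article's own premises (sinonasal gain expected, pulmonary effect uncertain) make a divergence plausible with accurate answers throughout. Misreading can go either way: genuine benefit taken for bias when FEV1 is flat, or bias overlooked when FEV1 rises.

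The size can only be illustrated. The rates of about 78% to 87% and 15% to 25% depend on the assumed flag rule, 1:1 groups, and effects back-solved from the article's power statements. That the check cannot tell t from b depends on none of these; it needs only that no known relation ties the FEV1 effect to the true questionnaire effect.

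The consequence is for how Objective 2 results are interpreted. The change is worth making because closer comparators are already being collected.

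**What to change.** 1. Drop FEV1 as the yardstick for self-report bias, or limit it to the respiratory content of CFQ-R.
2. Compare change in QOD with change in SIT at all follow-up visits, and change in SNOT-22 with change in endoscopy score from baseline to month 6. State that Lund-Kennedy scoring applies at both endoscopy visits; the article describes it only under Baseline measures.
3. In each comparison, estimate the ESS-versus-CMT difference in questionnaire change adjusted for objective change, with the interaction as a secondary look.
4. Report the result as supportive, not as proof of bias. Objective change is itself a post-treatment variable, so the groups can differ at a given objective change for reasons other than reporting.
5. State that PHQ-9, PSQI and CFQ have no objective comparator in the study, so reporting bias in them cannot be checked.
6. List SIT as an objective test in Statistical methods, in line with Outcome assessments.

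Cost: wording only, since Table 3 already schedules these measures. The limits are that endoscopy ends at month 6, short of the 12-month endpoint, and may be scored by clinicians who know the treatment.

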Additionally, we will implement multiple approaches to compare changes in longitudinal treatment outcomes listed in objectives 1–3 between the ESS and CMT groups. First, multivariate Profile Analysis (MPA) [30], unlike the mixed model approach, can handle multiple variables simultaneously and does not require stringent assumptions. Two main effects from the MPA model are of interest: 1) Tests on patient group differences at baseline on the outcomes in the study and 2) tests of “parallelism”, determining if the outcome trajectories (or profiles) change similarly in the two patient groups over time. Second, we will apply Propensity Score Matching (PSM) to test for the causal effects of ESS and CMT on study outcomes, and to create balanced treatment comparisons to address self-selection biases [31, 32]. Other methods using propensity scores like weighting or stratification, and instrumental variable (IV) approach, will also be considered to adjust for potential biases and estimate causal effects.

Consideration was given to restricting enrollment to surgically naïve patients; however, this approach would limit enrollment. We will therefore explore subgroup analyses in surgically naïve study participants and sensitivity analyses to look at changes over time in outcomes. We also plan to account for surgical history in a mixed effects model that includes previous sinus surgery.

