### Patient retention and missing data analysis

Missing data will be presumed to be missing at random (MAR). For our primary analyses, we will use mixed effects model to handle missing data issues based on MAR using Full Information Maximum Likelihood (FIML) estimation.

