## Discussion

In this multi-institutional prospective study, our primary objective is to evaluate post-ESS outcomes in PwCF+CRS in the era of highly effective modulator therapy. We will examine pulmonary function, PEx rates, antibiotic use, QOL, productivity loss, and health utility value over a 12-month period post-ESS. Our study uniquely will compare the impact of HEMT on outcomes between PwCF+CRS who undergo ESS and those opting for CMT.

Our study leverages a prospective, multi-institutional design, mitigating the limitations of small sample size and common biases associated with retrospective review. We acknowledge the limitations of an observational design instead of a randomized controlled clinical trial (RCT). This design was selected based on challenges of randomizing surgical interventions and PwCF’s reservations about randomization to ESS or delayed intervention [35]. Many PwCF expressed reluctance to be randomized, which would likely have led to enrollment difficulties in a RCT [35]. Further, there are notable difficulties in randomizing study participants to surgical interventions that require general anesthesia. These include the high cost of interventions that the study may have to fund (ESS estimated at > $10,000 USD/case) [36] and ethical considerations, such as employment of sham surgery in a placebo control arm [37]. To minimize potential bias, we will employ advanced statistical techniques like MPA and propensity score matching. Our method is poised to produce robust data, including endpoints that can provide some of the first insights of CRS outcomes in the current era. Data accumulated from this study will provide preliminary data upon which to design future trials.

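### The stated reason for adding multivariate profile analysis does not hold against this plan's own mixed model, its two tests are mislabelled, and it is credited with bias control it does not provide

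*Protocol article*

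**What the plan says.** The Statistical methods section first sets out mixed effects models. For ppFEV1 the listed fixed effects are baseline FEV1 in three bands, CF variant status, modulator use, sex, prior sinus surgery, time and treatment. No treatment-by-time term is named. On covariance it says: "An unstructured variance approach will model within-subject errors".

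It then goes further: "Additionally, we will implement multiple approaches to compare changes in longitudinal treatment outcomes listed in objectives 1–3 between the ESS and CMT groups". The first of these approaches is MPA, which, it says, "unlike the mixed model approach, can handle multiple variables simultaneously and does not require stringent assumptions". Two MPA results are of interest, and both are called main effects. The first is "Tests on patient group differences at baseline on the outcomes in the study". The second is parallelism, described as "determining if the outcome trajectories (or profiles) change similarly in the two patient groups over time". Propensity score methods follow as the second approach, and self-selection is assigned to them.

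The missing-data section presumes missing at random (MAR) and continues: "For our primary analyses, we will use mixed effects model to handle missing data issues based on MAR using Full Information Maximum Likelihood". It does not mention MPA. The Discussion, on the limits of a non-randomized design, says: "To minimize potential bias, we will employ advanced statistical techniques like MPA and propensity score matching".

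**The concern.** Patients choose surgery or continued medical therapy, so baseline comparability and confounding are the main threats to validity. The plan presents MPA as a check that is lighter on assumptions than the mixed model and that helps to reduce bias. If neither is true, a disagreement between the two analyses would be misread in favour of the weaker one, and agreement would be taken as reassurance about confounding that MPA cannot give. If the usual MPA group test were run and reported under the label in the text, a treatment effect could be reported as baseline imbalance, or a real imbalance could be missed.

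**Working it through.** The plan gives no figure for MPA, so there is none to reproduce. The check compares assumptions and then simulates. From the article: five visits (baseline, 3, 6, 9 and 12 months), 150 patients, two-sided 5% level. Assumed: SD 1 at each visit and correlation 0.7 to the power of the visit lag. Rejection rates come from 3,000 replicates.

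**1. Assumptions side by side**

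| Requirement | Classical MPA | Planned mixed model |
|---|---|---|
| Normality | multivariate normal | normal (Gaussian form) |
| Covariance over visits | unstructured | unstructured |
| Same covariance in both groups | yes | yes, if one common matrix is fitted |
| Common visit times | yes | no |
| Complete data for each patient | yes | no, under MAR with full-information likelihood |

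MPA is lighter only than a model with a restricted covariance such as sphericity, and that is not the model planned.

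The shared equal-covariance assumption matters. Parallelism was tested by Hotelling's T² on the p = 4 changes from baseline: T² = [n1·n2/(n1+n2)]·m′S⁻¹m, and F = T²·(n1+n2−p−1)/[p·(n1+n2−2)], with m the difference in mean change vectors and S the pooled covariance. With no group difference it rejected in:
- 5% with equal covariances;
- 11% with groups of 50 and 100 and an SD ratio of 1.5, the larger SD in the smaller group;
- 19% with the same groups and a ratio of 2;
- 1.4% with groups of 100 and 50 and a ratio of 1.5, the larger SD in the larger group.

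A mixed model with one common covariance has the same weakness, so MPA is no remedy for it.

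**2. What the usual group effect tests**

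Let b be a lasting baseline difference and δ a constant effect at the four follow-up visits. The average over visits has expected difference [b + 4(b + δ)]/5 = b + 0.8δ. With 75 per group:
- b = 0, δ = 0.5 SD: expected difference 0.40 SD. The averaged test rejected in 88%, a baseline-only t-test in 5%.
- Baseline difference 0.5 SD, then −0.125 SD at each later visit: (0.5 − 4 × 0.125)/5 = 0. The averaged test rejected in 5%, the baseline-only test in 86%.

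**3. Self-selection**

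With no treatment effect and treatment choice depending on the baseline value:
- log-odds 0.5 per SD: parallelism rejected in 28%, spurious difference in 12-month change −0.36 SD;
- log-odds 1.0 per SD: 75% and −0.63 SD.

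The cause is regression to the mean, which unadjusted MPA reads as non-parallel profiles.

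**4. Incomplete patients, only if MPA were run on complete cases**

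The true effect was 0.50 SD, with 80% to 83% of patients complete. Three MAR dropout mechanisms gave complete-case estimates of:
- 0.50, dropout driven by the current level;
- 0.44, driven by the change so far, in the same direction in both groups;
- 0.15, driven by the change so far, in opposite directions.

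Full-information likelihood gave 0.50 each time. The bias depends wholly on the mechanism.

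**5. What a covariate must do in the replacement test**

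Suppose the baseline visit is among the responses, the data are complete and the covariance is unstructured. A covariate entered only as a main effect shifts all five visits equally and cancels from every change, so the group-by-visit estimate equals the raw difference in mean change. To adjust that estimate, the covariate needs its own by-visit terms, or the follow-up visits must be modelled conditional on baseline.

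**The case against.** The strongest reply is that MPA is introduced as an addition, that no primary estimate or sample size depends on it, and that self-selection is assigned to propensity scores in the same paragraph. This stands and limits the severity. It does not rescue the Discussion sentence, which names MPA beside matching as a means of reducing bias.

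Second, the baseline test can be taken literally as a contrast at baseline, which would be correct and is obtainable under suitable coding. That reading is possible. The harm in step 2 arises only if the standard group effect is run under that label, but calling the test a main effect of MPA invites exactly that. Calling parallelism a main effect is a slip of terms, since its content is described correctly.

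Third, handling several outcomes jointly is a true property of MPA, and no joint mixed model is described. This is fair as far as it goes, though mixed models can also be fitted to several outcomes. The plan also promises to verify model assumptions, but that does not make the comparative claim true.

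Two stronger readings are tempting and are not supported:
- A reader might infer that MPA drops incomplete patients and so contradicts the MAR plan. Listwise deletion is the classical default, but the article does not state it. Likelihood or imputation versions exist, and the full-information rule is tied to the primary mixed models.
- A reader might infer a loss of power below the sample size target. The stated 20% dropout alone leaves 0.8 × 150 = 120 complete patients, above the 106 required. Falling below 106 needs intermittent missingness that the article does not give, and even 5% per follow-up visit leaves 0.8 × 0.95⁴ × 170 = 111 at the anticipated enrolment. The 106 is also not stated to size MPA, whose parallelism test has several degrees of freedom.

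**Conclusion.** The point holds in limited form. MPA's assumptions are not weaker than those of the planned mixed model; in classical form it adds complete data and common visit times. The plan's labels do not match the usual MPA tests. As described, MPA has no adjustment for self-selection, so it cannot support the bias claim in the Discussion.

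The 0.8 share is exact for a constant effect at four of five visits. The rejection rates rest on the assumed SD, correlation, group sizes and selection strengths; they show direction and possible size and do not predict this study's results. The severity is minor to moderate because MPA is supplementary. Neither a conflict with the MAR plan nor a power shortfall is part of the conclusion.

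**What to change.** - Add the group-by-visit interaction to the full-information mixed model and make it the test of parallelism, with the planned covariates. Give the covariates thought to drive treatment choice, including the baseline value of the outcome, their own by-visit terms, or model follow-up visits conditional on baseline.
- Test baseline differences with a baseline-only contrast.
- Delete the claim that MPA avoids stringent assumptions.
- If MPA is kept, label it an unadjusted supportive analysis, state its assumptions and its handling of incomplete patients, and name its tests levels (averaged over visits) and parallelism (an interaction).
- Remove MPA from the bias sentence in the Discussion, leaving the propensity score methods.

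The cost is a few sentences and some extra terms in a model already planned. Each by-visit covariate uses a few degrees of freedom. No new data, visits or patients are needed.
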